**Fig. 2 Fig2:**
[figure not shown]
Planned data collection periods

###  Data sources

The data for the evaluation will be gathered from two main data sources. Firstly, various reports will be generated from the digital interactive health diary. These reports will encompass health-related basic data entered by participants, their caregivers, and their primary care physicians, such as current condition, diagnoses, therapies, medication plans, level of care needed, allergies, and measured vital parameters. Additionally, questionnaires for process evaluation and evaluation of health and quality of life will be collected via the digital interactive health diary as well as via the online platform SoSci Survey. Furthermore, all data for the STH event will be extracted through digital interactive health diary reports for the evaluation of utilization patterns and costs, as well as for process evaluation.

As a second data source, data from the health insurance companies will be utilized (enrollee data, claims data concerning sick pay, nursing care, short-term care, outpatient and inpatient cases, ambulance services, prescription of medicinal products, medical devices, and aids). This will be used to establish the control group 1 and to obtain data for comparing the new form of healthcare with standard care.

The reports from the diary are continuously accessible in pseudonymized form by the evaluating parties. Each evaluation party receives only the data necessary for their specific research questions. For the evaluation utilization patterns and costs, it is necessary to merge the data from the diary with the enrollee and billing data from the health insurance companies. This is because treatments provided by the mobile medical on-call service within the framework of STH events are partly reimbursed and documented through STH project funds and partly through statutory health insurance.

Data collection forms cannot be provided here. However, all variables and their response formats are described within the protocol.

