###  Intervention

The new form of healthcare Stay@Home – Treat@Home (STH) focuses on establishing an interdisciplinary and trans-sectoral network for low-threshold outpatient care in the home of care dependent individuals. This is facilitated through the digital interactive health diary, a telemedical application. Here, information about the participants' health status is collected by themselves, their caregivers, their general practitioner, and all stakeholders involved in acute care within the new form of healthcare and is accessible by them when needed [16]. The new form of healthcare covers two areas of care: primary care as well as acute and emergency care.

The primary care takes place as long as participants are in a stable health condition without acute care needs. Their health status is regularly recorded and reviewed by themselves, their caregivers, and their primary care physician within the digital interactive health diary.

Acute and emergency care comes into play when regular entries in the digital interactive health diary enable the early detection of deteriorating health conditions. Initially, participants or their caregivers contact their general practitioner (GP), who then provides care to the participants as part of standard care. If the general practitioner is unreachable, participants call the medical on-call service of the Berlin Association of Statutory Health Insurance Physicians (KV Berlin) using a special hotline stored in the digital interactive health diary, thereby activating the care network. This triggers an STH event. The medical on-call service center determines the current care needs based on the symptoms of the patient/participant as well as their entries in the digital interactive health diary using the Structured Initial Medical Assessment in Germany (SmED) [17]. The care pathways are outlined in Fig. 1.

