For the control group from the health insurance data (control group 1), insured individuals with similar characteristics to those in the intervention group will be identified from the enrollee and billing data of the participating health insurance companies. For better comparability, the aim is for the control group to also originate from Berlin, Germany. However, if the numbers are not sufficient, patients from structurally similar settlement areas will be included in the control group. A minimum 1:1 matching is planned, ensuring that the control group will be the same size as the intervention group. Depending on the number of insured individuals in the participating health insurance companies, a 1:n matching may also be performed, thereby increasing the size of the control group accordingly.

The control group for the secondary outcomes (control group 2) will be *n* = 300.

The rationale of this study is to select control groups that do not receive the intervention and an intervention group that does. It is based on the study's objective to assess the efficacy of the intervention in comparison to no treatment. For the control group 2 individuals with similar characteristics to those in the intervention group, but being insured by other than the participating health insurance companies, will be included in the study. This design allows it to determine the direct impact of the intervention by observing differences between the groups. The use of two no-intervention control groups is ethically justifiable in this context, as the expected benefits of the intervention are hypothesized but not yet established. This approach ensures that any observed effects can be attributed specifically to the intervention, thereby providing clear insights into its potential benefits.

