**Patient perspective**			
Health	QoL-AD; own design of questions	Diary data and SoSci Survey	secondary
Well-being	WHO-5; OSSS-3; UCLA-LS	Diary data and SoSci Survey	secondary
Care dependency	Barthel-Index	Diary data and SoSci Survey	secondary

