**Healthcare provider perspective**			
Interdisciplinary cooperation	Own design of questions	Diary data	secondary
Suitability of tasks	Own design of questions	Diary data	secondary
Usability	BGW	Diary data	secondary

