##  Discussion

Demographic change leads to a larger population of older individuals and consequently more people facing mobility issues and care dependency. Furthermore, the shortage of nursing staff and other medical personnel will exacerbate the situation [40]. New forms of care are needed to facilitate the work of healthcare providers and improve the health of care recipients. Advances in medicine and technology can help maintain or even improve the quality of life among the growing older people population [41]. With Stay@Home – Treat@Home, care dependent individuals can be monitored for health at home and provided medical services. Supported by a closely coordinated care network spanning both outpatient and inpatient sectors, and leveraging state-of-the-art technologies and telemedicine, the aim of the study is to evaluate whether this approach leads to a reduction in hospital admissions [42] and alleviate the burden on the healthcare system [43].

The digital interactive health diary serves various functions. Firstly, it facilitates direct communication among patients, their caregivers, and healthcare providers. Regular entries related to health queries and measurements are guided and monitored by the GP. The GPs can access the health documentation stored by patients and caregivers at any time, allowing to remotely monitor the patient's condition. Secondly, patients and their caregivers can more easily detect any changes in health status themselves and take appropriate measures [44]. Thirdly, should an intervention be necessary at the patient's home, personnel of nursing aid services as well as physicians can also access the entries to gain an understanding of the patient's health trajectory. They can document the measures they have taken, thereby providing a record of the course of events for all other healthcare providers involved.

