###  Limitations

The approach to recruitment or data access for the intervention and control group 1, respectively, will be different, which can cause different selection bias in the intervention and control group 1.

A further aspect of the study, which contributes to the selection bias is, e.g. the fact that the study will only be conducted in Berlin. Therefore, regional differences cannot be considered and the generalization of the results to rural areas must be approached with caution. Only participants with a caregiver or members of participating health insurance companies can be included in the study, which may also lead to a certain selection bias. However, part of the bias is taken into account by including persons who are insured with a health insurance company that is not participating in the project in control group 2 with regard to the survey on the secondary endpoints. Additionally, for ethical and practicality reasons, a randomized controlled trial cannot be implemented.

There is also a possibility of a measurement bias, if the billing data is not maintained carefully by the responsible organizations. A response bias is possible in the data coming from the digital interactive health diary.

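### Patient-reported outcomes are collected by two modes, and only the intervention group has the diary, so collection mode is tied to group in the comparison with control group 2

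*Protocol article*

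**What the plan says.** - **Modes.** Data sources states that questionnaires for "evaluation of health and quality of life will be collected via the digital interactive health diary as well as via the online platform SoSci Survey". Table 1 gives "Diary data and SoSci Survey" as the source for health, well-being and care dependency. Its provider rows ("Own design of questions" or the BGW questionnaire) list the diary alone.
- **Who has the diary.** The Intervention section says of the care network: "This is facilitated through the digital interactive health diary, a telemedical application". The Participants section gives the rationale as to "select control groups that do not receive the intervention and an intervention group that does". The same section holds that this approach lets observed effects be ascribed to the intervention itself.
- **What the diary is used for.** The on-call service draws on diary entries to determine care needs (Intervention). The Discussion says that GPs oversee the regular health entries and adds: "The GPs can access the health documentation stored by patients and caregivers at any time".
- **The comparison.** Outcomes, Patient perspective, plans a pre-post comparison of the intervention group with control group 2 (300 people). The scales are given at weeks 2-4 and at 3-6 months, and seven health questions are put weekly to both groups. Analysis, Patient perspective, leaves the regression model to be chosen later.
- **Acknowledged limitation.** "A response bias is possible in the data coming from the digital interactive health diary". The Limitations section does not say that this bias would fall on one group only.

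**The concern.** A comparison of self-reported scores is clean only if both groups answer in the same way. Here one mode is a working part of the treatment. Someone entering answers in an application that the care network uses may answer differently from someone filling in a research survey, because the setting, the available help and the possible consequences of an answer differ. If mode follows group, a mode difference and a treatment effect look the same in the data, and no model can separate them afterwards.

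This is the only planned between-group comparison for quality of life, well-being, loneliness, social support and care dependency. The study objective names several of these. The article's claim that effects can be attributed to the intervention would not hold for these outcomes if the modes differ.

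**Working it through.** The article states no figure on this point, so the check has a textual part and an illustrative part.

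**Is mode tied to group?**

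1. Both modes are listed for every patient outcome, with no split by group.
2. The diary belongs to the intervention, and control group 2 does not get the intervention. Diary answers therefore come from the intervention group only.
3. SoSci Survey appears only in the Table 1 rows that involve control group 2. This fits its being that group's form, but it is an inference.
4. If all intervention participants use the diary, mode and group coincide. If only a fraction p do, a constant shift b moves the group mean by p × b. For example, p = 0.5 and b = 0.20 SD give 0.10 SD. Mode is tied to group in either case; only the degree differs.

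**How large must a shift be to matter?**

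Inputs: 1,500 and 300 people (article), two-sided 5% test, normal approximation, everyone responding. Assumptions: constant mode shift b of 0.05 to 0.30 SD, pre-post correlation r of 0.5 or 0.7, no true effect. The article gives neither b nor r.

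- Single time point: SE = sqrt(1/1500 + 1/300) = 0.0632 SD, and 1.96 × 0.0632 = 0.124 SD. With 1,210 in the intervention group the SE is 0.0645, so its size hardly matters; the 300 controls dominate.
- Post-only comparison: bias b, SE 0.0632.
- Baseline-adjusted regression: the same shift sits in both measurements, so the bias left is b(1 − r), with SE 0.0632 × sqrt(1 − r²). For b = 0.20 and r = 0.5: bias 0.10, SE 0.0548, ratio 1.83, rejection rate 45%.
- Difference of changes: bias b − b = 0.

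Two-sided false-positive rates:

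| Constant shift b (SD) | Post-only | Baseline-adjusted, r = 0.5 | Baseline-adjusted, r = 0.7 | Difference of changes |
|---|---|---|---|---|
| 0.05 | 12% | 7% | 6% | 5% |
| 0.10 | 35% | 15% | 10% | 5% |
| 0.20 | 89% | 45% | 26% | 5% |
| 0.30 | 99.7% | 78% | 51% | 5% |

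A shift can also hide an effect. In a post-only comparison, a true 0.20 SD effect with an opposite shift of 0.10 SD has power of 35% instead of 89%.

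**If the shift changes over time.** The difference of changes is then biased by the amount of change. Its SE is 0.0632 × sqrt(2(1 − r)), which is 0.063 at r = 0.5 and 0.049 at r = 0.7. A change in the shift of 1.96 × 0.063 = 0.12 SD or 1.96 × 0.049 = 0.10 SD between the two surveys would reach p<0.05 by itself.

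**The case against.** The strongest reply has four parts.

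- **The assignment of mode to group is not stated.** An article may leave such operational detail to the full protocol. This stands in part: exclusive use of one mode per group is an inference, and full confounding is conditional on it. But that diary answers come only from the intervention group follows from two statements in the article, and nothing in it commits to a common form.
- **The care team is not said to see the scales.** A reader might infer that intervention participants report mood or loneliness to their GP and caregivers, with caregiver help, while controls answer an anonymous survey. The text does not support this. Data sources separates the basic health data entered by caregivers and GPs from the questionnaires, and the access statements speak of health information in general. The article says that participants carry out the Barthel assessment. Nothing calls the SoSci survey anonymous, and Data Storage describes anonymized collection for participants generally. The point does not need these claims: a difference in platform and reporting setting is enough.
- **The design is pre-post, so a constant shift cancels.** This is correct for a difference of changes, and it also holds for the weekly questions if they are analysed as change from the first weeks. It fails for the post-only and baseline-adjusted models that the article leaves open, and for a shift that changes over time. The article gives no evidence that such a change occurs.
- **Response bias is already disclosed, and only secondary outcomes are involved.** Both are true. The disclosure does not say that one group alone would carry the bias.

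**Conclusion.** The point holds in a limited form. As described, collection mode is associated with group for QoL-AD, WHO-5, OSSS-3, UCLA-LS, Barthel and the weekly health questions, and it is fully confounded with group if each uses one mode only. How much harm follows depends on three things that the article does not give: the share of the intervention group answering in the diary, the size and stability of any mode shift, and the analysis model. Under an assumed constant shift of 0.20 SD with full separation of modes, the false-positive rate runs from 5% (difference of changes) through 26% to 45% (baseline-adjusted) to 89% (post-only).

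A reader might conclude that these comparisons are certain to be biased, or that the trial's main result is in doubt. Neither follows. No mode shift has been shown, and the primary utilization and cost outcomes do not rest on these questionnaires. The point goes beyond a request for detail because, if modes are fully separated, it can be repaired only at data collection.

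**What to change.** 1. Collect QoL-AD, WHO-5, OSSS-3, UCLA-LS and Barthel on the same SoSci Survey form in both groups. The diary may send the link.
2. Record for every questionnaire, in both groups, the mode used and whether a proxy answered.
3. Flag scale answers already given in the diary, so that they can be set aside in a sensitivity analysis.
4. Put the weekly questions on the common form too. Otherwise report them descriptively or analyse them only as change from the first weeks, which removes a constant shift but not a changing one.
5. State the mode by group, and add any remaining difference to the Limitations, saying which group it affects.

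The cost is small, since SoSci Survey is already in use and 36 of the planned 1,500 participants were enrolled at submission. The price is that intervention participants, who are care dependent and 60 or older, open a second platform twice. That may slightly raise non-response, so response rates should be reported by group.

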###  Data Monitoring

The present study does not require a Data Monitoring Committee (DMC) due to its design and the nature of the intervention. The study involves a low-risk intervention with well-established safety profiles and outcomes. The potential for adverse events is minimal, therefore the need for ongoing oversight is not justified. Instead, regular internal oversight measures to ensure adherence to protocol and monitor data quality throughout the study will be implemented.

These are also the reasons, why this study does not require formal auditing of trial conduct. The internal oversight mechanisms in place will adequately ensure that the trial is conducted according to established guidelines and standards.

###  Data Storage

Personal information about potential and enrolled participants will be collected through secure, anonymized data collection methods, ensuring that identifiers are removed whenever possible. Data will be stored in password-protected databases with restricted access to authorized personnel only. During the trial, any sharing of personal information will be limited to essential personnel involved in the research, and all data will be shared in aggregated or de-identified form whenever feasible. A trusted third-party organization will be involved to link data while maintaining confidentiality and ensuring that sensitive information is protected. After the trial, all personal information will be maintained in a secure location for a designated period, and then permanently deleted, in compliance with data protection regulations.

###  Outcomes

Within the evaluation, three perspectives will be considered: health insurance, patients, and health care providers. All outcome variables are shown in Table 1.

**Table 1 Tab1:** Outcomes

**Outcome**	**Operationalization**	**Data source**	**Outcome type**

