###  Participants

 Assuming that the hospitalization rate in the patient group before the intervention is approximately 20 percent [2] with a potential of reduction to 15 percent during intervention (a reduction of 25 percent), with a power of 90 percent and a significance level of 0.05, the calculated sample size is 1,210 patients for the intervention group [18]. To address sample attrition due to heightened mortality in the research group as well as other unforeseeable drop-outs, about 25 percent additional patients should be recruited, resulting in a total sample size of *n* = 1,500 participants in the intervention group, with at least the same number of controls to be drawn. GPs will be recruited through outreach by the KV, which in turn will recruit eligible participants for the study. Alternatively, the participants will be recruited by a study physician to relieve the GPs. The informed consent will be obtained from the participants by either their GP or the study physician. The intervention group will be derived from eligible insurees of the participating health insurance companies, who are 60 years or older, reside in Berlin in their own home, receive support from a caregiver, and have been either officially granted “care level” 1 or higher, have applied for it or been assessed by their GP as needing “care level” 1 or higher. In Germany, five “care levels” represent a scale used to classify the level of care needed by individuals requiring long-term care. The respective care level determines the subsidies those individuals receive through their nursing care insurance provider. Participants can withdraw their consent to participate in the study anytime. If participants stop meeting the inclusion criteria listed above at some point, e.g. leave their participating insurance company, they will be excluded from the study.

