**Health insurance perspective**			
Utilization: Hospital stays and emergency responses	Number of hospital stays/ emergency responses	Claims data	primary
Utilization: Ambulatory-care sensitive hospital stays and emergency responses	Ambulatory-care sensitive diagnoses	Claims data	primary
Utilization: ambulatory resource allocation	Ambulatory medical utilization	Claims data	secondary
Cost: New form of healthcare	All costs directed towards the new form of healthcare	Diary and claims data	primary
Cost: Comparison of new form of healthcare versus standard care	Comparison with saved costs of standard care	Diary and claims data	primary

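### Table 1 contains no mortality outcome, although the plan expects heightened mortality and its primary outcomes can fall when patients die at home or a needed admission is missed

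*Protocol article*

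**What the plan says.** The Outcomes section of the protocol article closes the list: "All outcome variables are shown in Table 1". Four rows of Table 1 are marked primary, all under the health insurance perspective:

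- hospital stays and emergency responses, operationalized as "Number of hospital stays/ emergency responses";
- "Utilization: Ambulatory-care sensitive hospital stays and emergency responses";
- programme cost, operationalized as "All costs directed towards the new form of healthcare";
- the cost comparison, operationalized as "Comparison with saved costs of standard care".

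The secondary rows cover outpatient utilization, patient-reported health, well-being and care dependency, and provider cooperation and usability. The narrative on the health insurance perspective adds days in hospital. Neither the table nor the narrative names death or survival.

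Mortality appears in two other places. The Background lists it among the consequences of hospitalization for older care recipients with cognitive impairment. The Participants section gives it as a reason for recruiting more patients: "To address sample attrition due to heightened mortality in the research group as well as other unforeseeable drop-outs". The Data Monitoring section dispenses with a monitoring committee on the ground that "The study involves a low-risk intervention with well-established safety profiles and outcomes".

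**The concern.** The objective is fewer emergency situations and fewer unplanned admissions. The programme pursues it by handling suitable acute cases at home, so the harm specific to it is an admission that was needed and did not happen. Such a patient adds no stay, no hospital days and no inpatient cost. A patient who dies early also stops adding to all three. On the primary outcomes these cases look the same as an admission that was rightly avoided.

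Mortality against control group 1 is the obvious complementary measure, and the plan does not have it. A finding of lower utilization and cost could then be read as benefit without the one comparison that would qualify it. The omission also works against the programme: if avoiding hospital lowers mortality, as the Background suggests it might, the study would not show that either.

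**Working it through.** **1. The plan's own figure.** Inputs from the Participants section: 20% hospitalized before the intervention, 15% targeted, power 90%, significance level 0.05, 1,210 patients. Two-sided, unpooled variance:

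n = (1.960 + 1.2816)² × (0.20 × 0.80 + 0.15 × 0.85) / 0.05² = 10.507 × 0.2875 / 0.0025 ≈ 1,209 per group.

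The pooled version gives 1,212. The stated 1,210 is reproduced. The increase to 1,500 allows for total losses of 290 / 1,500 = 19.3%, deaths and other drop-outs together. No separate mortality rate is given.

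**2. How far can excess deaths alone move the primary utilization outcome?** Assumptions: the 20% is an annual risk, so the hazard while alive is h = −ln(0.80) = 0.223 per year; the intervention has no effect on it; follow-up is one year; deaths occur at constant hazard m = −ln(1 − annual mortality). Control mortality of 5 to 20% per year is assumed.

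- Share hospitalized: h / (h + m) × (1 − e^−(h+m)).
- Stays per enrolled person: proportional to mean time alive, (1 − e^−m) / m.

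Example, 10% versus 15% deaths:

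- Control: m = 0.105; share = 0.223 / 0.329 × (1 − 0.80 × 0.90) = 19.0%; time alive = 0.10 / 0.105 = 0.949 years.
- Intervention: m = 0.163; share = 0.223 / 0.386 × (1 − 0.80 × 0.85) = 18.5%; time alive = 0.15 / 0.163 = 0.923 years.
- Ratios (from unrounded values): 0.973 for the share, 0.972 for stays per enrolled person.

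Over the assumed range of control mortality, 1,210 per group:

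| Excess deaths, intervention | Fall in share hospitalized or stays per person | Chance of a significant result favouring the intervention (share hospitalized) |
|---|---|---|
| 0 points | 0% | 2.5% |
| 5 points | about 3% | about 5% |
| 10 points | about 5 to 6% | 9 to 10% |
| 20 points | about 11 to 13% | 25 to 30% |

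For lost time at risk alone to produce the planned 25% reduction, intervention mortality would have to reach about 49 to 59%. The direction of the bias is clear; its size by this route is small beside the target.

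**3. Would anything in the plan show under-treatment against control group 1?**

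- Ambulatory-care-sensitive coding classifies admissions that took place. A missed one leaves no code.
- Health, well-being and Barthel data are compared with control group 2 (n = 300) only. The scales' second measurement, at 3 to 6 months, reaches only those still taking part.
- GP review and stakeholder ratings of events within the programme have no comparator.
- Reasons for discontinuation are collected to understand dropout, not as a comparison with control group 1.
- Participants who stop meeting the inclusion criteria are excluded. Living in one's own home is one criterion, so some who deteriorate leave the data.

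None of these compares deaths with control group 1.

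**4. Could the study estimate a mortality difference?** With 1,210 per group, the 95% half-width is 1.96 × √(2p(1 − p) / 1,210), which is 2.4 points at p = 0.10 and 2.8 points at p = 0.15. Power is 96% for 10% versus 15%, 84% for 20% versus 25%, and 49% for 10% versus 12.5%. These mortality rates are assumptions, and the figures cover random error only.

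**The case against.** The best defence is that the artefact is small at plausible mortality differences, that person-time and handling of death are commonly settled in an analysis plan that is not shown, and that the care pathway has safeguards. Patients contact their GP first, triage is structured, emergencies leave the programme at once, a consulting physician can refer to hospital, and the GP reviews every event. All of this is correct. It limits the size of the concern, but an analysis plan that adjusts for time alive would still not make mortality an outcome, and the article presents its outcome list as complete.

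A reader might go further in four ways that the documents do not support.

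- *About 60 extra deaths would reproduce the whole planned effect.* The figure is 0.05 × 1,210 = 60.5. It restates the target and assumes that each excess death removes exactly one patient who would otherwise have been hospitalized. The time-at-risk calculation gives a far smaller effect.
- *Every primary outcome improves when a patient dies.* This assumes totals per enrolled person without regard to time alive. A death preceded by an ambulance call or admission adds events and cost, as does failed home care that ends in an emergency.
- *The study cannot tell avoided from missed admissions.* The weekly symptom questions, the Barthel-Index, the event ratings and the questions on detection and urgency give some information. What they lack is a comparison with control group 1.
- *The article contradicts itself on safety.* The Participants section calls the expected benefit unproven, while Data Monitoring speaks of safety. Both can be true together.

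Two practical objections stand. The Limitations section concedes that the two groups are reached by different routes, so a mortality comparison will be confounded. And 36 participants had been enrolled by submission, with recruitment ending in June 2025, so 1,210 per group is not assured.

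**Conclusion.** The point holds. Mortality is absent from an outcome list declared complete, in a population where the plan itself expects raised mortality and for an intervention whose success is measured by reduced use of acute care. Deaths at home or missed admissions can lower the primary outcomes, and no listed outcome compared with control group 1 would reveal it.

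The part that can be calculated is modest: about 3% per 5 points of excess mortality, against the planned 25%. It rests on constant hazards, one year of follow-up, an annual reading of the 20%, no adjustment for time alive, and control mortality of 5 to 20%. Undetected under-treatment is the larger concern and cannot be sized from the documents. Nothing in the article indicates that such harm is occurring, or that a reduction in utilization would necessarily be false.

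**What to change.** Add to Table 1, under the health insurance perspective, all-cause mortality from entry to end of observation, intervention group versus control group 1, with a matched index date for the controls. Take it from the enrollee data, after confirming that they record deaths, and use the same matching and adjustment as for the primary outcomes.

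Analyse stays, hospital days and costs with account of time alive, for example with days alive and out of hospital as a companion outcome. State in the Analysis section that any reduction in utilization or cost is reported together with the mortality difference and its confidence interval.

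The cost is a little more analysis. Enrollee and inpatient claims data are already requested, so no new patients or procedures are needed, and the Design section describes a route for protocol modifications. The drawbacks are that the mortality comparison shares the confounding of the non-randomized design and must be read with that caution, and that the headline claim can no longer be read without the mortality result.
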